#### Recruitment strategy

Within each of the communities, the study team will conduct recruitment events at partnering churches and community and senior centers, with the goal of recruiting individuals representing the ethnoracial diversity of the chosen communities. Participants will be recruited by community research assistants (CRA) who have personal knowledge of these communities, including their places of worship, neighborhood community centers, and parent-teacher associations (several current CRAs are local educators, in addition to social workers, pastoral leaders, and other trusted gatekeepers).

Adjustments to the recruitment strategy will be made carefully and in response to opportunities that would be consistent with the study aims or due to unexpected recruitment issues. The study will be advertised via flyers and word of mouth. Enrollment will be guided by ADRD Research Recruitment principles: (1) fostering existing community partnerships, (2) building on trust to share ownership of the research mission, and (3) welcoming new partnerships based on community needs. The study embraces the principle of increasing workforce diversity and community bridges between university and community settings by hiring residents as CRAs. During participant recruitment activities, we will offer clinical measurements [e.g. HbA1C (6-month blood glucose) and body mass index (BMI)] in partnership with Healthier Glades and the local Diabetes Coalition.

#### Informed consent

If a potential participant is eligible and willing, they continue with the consent procedures using the e-consent form in REDCap. All participants receive a written copy of the consent form in their preferred language (English, Spanish, or Haitian Creole). The consent process consists of a conversation in which a bilingual member of the research team reviews the consent form, answers questions, and confirms their willingness to participate by reading the consent statement aloud. Additionally, they will be asked if they would be willing to participate in future studies. The CRA will confirm the participant’s response and indicate in REDCap that informed consent was obtained. If the enrollee affirms additional interest in participating in either the smartwatch or air pollution monitor subsample, this will also be indicated in REDCap for potential future follow-up. When subsample participants are consented, they will be asked to consent using a separate consent process with a subsample consent form which is also documented in REDCap.

#### Participant incentives

All participants will receive one $25 gift card for completing the initial research activities (enrollment and baseline data collection). Those who return for annual and follow-up visits will receive a $25 gift card after each visit. A purposive sample of 120 persons distributed throughout the five communities will be offered a $25 gift card for each month of smartwatch monitoring (2 months total). Thirty-six participants who agree to host low-cost PM_2.5_ sensors (i.e., PurpleAir monitors) monitors will receive a one-time additional gift card worth $20.

#### Timeline of study assessments

For the 36-month study, at the baseline visit (T0), which occurs immediately after consent, individuals will provide data on sociodemographics, health history, and health behaviors. Participants will return to complete six-month follow-up visits for a total of seven visits (baseline and six follow-ups). During each follow-up visit (T1-T6), individuals will complete the cognitive and mini-physical performance assessments, biomarkers (e.g., blood pressure, BMI), and PROMIS measures targeting perceptions of social isolation, alcohol use, anxiety, depression, sleep problems, physical function, fatigue, ability to participate socially, and degree of pain interference with activities of daily living. The first participant was enrolled on January 20, 2024.

For the smartwatch sub-study, participants will wear an Apple Watch SE for 2 four-week periods, one during burn season and one during a non-burn period. Social isolation and cognitive function will be assessed during both the burn and non-burn seasons to identify potential changes in response to smoke-related air pollution (PM_2.5_). These outcomes are critical for understanding the health impacts of air pollution on cognitive and social well-being. Built and social environments (e.g., park spaces and ethnoracial composition) will be characterized at baseline and repeated if more current addresses or data become available during the study. Air quality monitoring will be continuous throughout the 36-month period. Table 1 shows the schedule of assessments and instrument collection by visit.

**Table 1 pone.0312660.t001:** Data collection schedule for 36-month study.

Data collected	T0^d^	T1 6 mo.	T2 12 mo.	T3 18 mo.	T4 24 mo.	T5 30 mo.	T6 36 mo.
ADRD assessment (MoCA v.8.1–8.3 and Cognigram)^a^		X	X	X	X	X	X
Sociodemographics^b^	X	X	X	X	X	X	X
Health conditions/behaviors^b^	X	X	X	X	X	X	X
Blood pressure, height, weight^a^		X	X	X	X	X	X
Mini Physical Performance Test (mini PPT)^a^		X		X		X	
Psychosocial measures (e.g., isolation)^b^		X	X	X	X	X	X
Anxiety, depression^b^		X	X	X	X	X	X
Sleep problems^b^		X	X	X	X	X	X
Physical function, fatigue, pain interference^b^		X	X	X	X	X	X
Ability to participate socially		X	X	X	X	X	X
Alcohol use^b^		X		X		X	
Air pollution monitors^c^	X	X	X	X	X	X	X

FU = Follow-up; mo = month; ^a^ From clinic assessment; ^b^ From questionnaire; ^c^ Monitors distributed at key sites within communities; ^d^ Screening visit

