**Methods:**

We will recruit 1,087 community-dwelling, dementia-free, ≥45-year-olds from five communities in Florida’s Lake Okeechobee region. Over 36 months, participants will complete baseline visits to collect demographics, health history, and health measurements (e.g., blood pressure, body mass index) and 6-month follow-ups assessing cognitive function and social isolation at each visit. A subsample of 120 participants representative of each community will wear smartwatches to collect sensor data (e.g., heart rate) and daily routine and predefined activities (e.g., GPS-captured travel, frequent destinations) over two months. Ecological momentary assessments (EMA) (e.g., whether smoke has bothered participant in last 30 minutes) will occur over two months during agricultural burning and non-burning months. PurpleAir monitors (36 total) will be installed in each community to continuously monitor outdoor PM_2.5_ levels.

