#### Specific aims

Aim 1. Examine the contribution of particulate matter <2.5μm (PM_2.5_) exposures to social isolation and cognitive function (CF), through multilevel growth modeling.

Aim 1a. Examine baseline levels and growth trajectories of SI and CF associated with changes in PM_2.5_ during agricultural burn and non-burn seasons over a 36-month period, accounting for individual- and neighborhood- level characteristics.Aim 1b. Examine the effect modification of race/ethnicity on the relationship of PM_2.5_ on baseline levels and growth trajectories of SI and CF, accounting for individual- and neighborhood-level characteristics.

Aim 2. Determine the effects of the built environment (e.g., retail destinations, park space) and social environment (e.g., crime, SES) on SI and CF through linear mixed modeling.

Aim 2a. Examine SI and CF associated with the built and social environment over a 36-month period (baseline, and FY 1,2,3), controlling for individual- and other neighborhood-level characteristics.Aim 2b. Explore the effect modification of race/ethnicity on the relationship of the built and social environment with SI and CF, in view of their educational and social disadvantage.

Aim 3. Contextualize SI and CF among residents from different ethnoracial groups using EMA and sensor- derived behavior models during burn and non-burn seasons in a subsample of 120 ethnoracially diverse participants, stratified by Lake O communities.

Aim 3a. Examine residents’ momentary changes in behavioral markers, mood, and cognitive performance, associated with changes in air quality and the social and built environment.Aim 3b. Characterize differences among ethnoracial groups and between women and men in their momentary changes in behavioral markers, mood, and CF performance in response to changes in air quality and the social and built environment.

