#### Psychosocial measures

At the T1 to T6 visits, the PROMIS Social Isolation 4a [50], Lubben Social Network Scale-6 (LSNS-6) [51], Berkman-Syme Social Network Index (BSNI) [52], and De Jong Gierveld Loneliness Scale will assess social isolation, social connectedness, and social networking, and loneliness, respectively [53].

PROMIS Social Isolation 4a: A brief tool with evidence of validity and reliability (Coefficient alpha > 0.90) assessing social isolation over the past seven days with four items (e.g., feel left out) rated from 1 (Never) to 5 (Always). The total score ranges from 4 to 20, with higher scores indicating greater social isolation.LSNS-6: An instrument with evidence of validity and reliability (Coefficient alpha > 0.80) assessing social engagement through six items (e.g., number of relatives see/hear from at least once a month) scored from 0 to 5. The total score ranges from 0 to 30, with lower scores indicating greater social engagement.BSNI: An instrument with evidence of validity and reliability (Coefficient alpha = 0.79), assessing social connectedness through 11 items (e.g., frequency attending religious meetings/services) measuring four types of social connections, including marital status (married versus not), sociability (number and frequency of contacts with children, close relatives, and close friends), church group membership (yes versus no), and membership in other community organizations (yes versus no). Scores range from 0 to 4, with higher scores indicating greater connectedness.De Jong Gierveld Loneliness Scale: An instrument with evidence of validity and reliability (Coefficient alpha ≥ 0.70–0.76) instrument that collects 6 items (e.g., miss having people around) that measure overall loneliness, including emotional and social loneliness, with responses ranging from "*yes*" to "*more or less*" to "*no*." The total score ranges from 0 to 6, with higher scores indicating greater loneliness.

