#### Aim 2A

General linear mixed model analyses of participants nested within neighborhoods (i.e., census block groups) will be used to examine the effect of built and social environments on CF and SI for Aim 2A. Primary analysis will model effects of the four domains of social and built environment and the HNI on baseline CF and SI and on changes over 36 months, accounting for random neighborhood-level variance. Both time-varying (e.g., health behaviors, work and home environments, comorbidities) and time-invariant (e.g., sex) individual- and neighborhood-level covariates (see Fig 1) will be incorporated into prediction models to control for these additional individual and neighborhood/community influences on outcomes.

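### Cognition and social isolation outcomes are first collected at T1 (month 6), yet Aims 1a and 2a and the Aim 2A primary analysis model baseline levels and 36-month change with baseline defined as T0

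*Protocol article*

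**What the plan says.** **Schedule.** Under Timeline of study assessments, "at the baseline visit (T0), which occurs immediately after consent, individuals will provide data on sociodemographics, health history, and health behaviors". The same section continues: "During each follow-up visit (T1-T6), individuals will complete the cognitive and mini-physical performance assessments". In Table 1 the rows "ADRD assessment (MoCA v.8.1–8.3 and Cognigram" and "Psychosocial measures (e.g., isolation" have no mark at T0 and are marked at every visit from T1 (6 months) to T6 (36 months). The section on T0 measures describes a survey only. The Cognitive measures section places testing at T1 to T6. The Psychosocial measures section opens "At the T1 to T6 visits, the PROMIS Social Isolation 4a" and lists LSNS-6, BSNI and the loneliness scale for the same visits. Baseline is identified as T0, and the seven visits are counted as baseline plus six follow-ups.

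**Analysis.** Aim 1a under Specific aims is to "Examine baseline levels and growth trajectories of SI and CF associated with changes in" PM2.5 over 36 months. Aim 2a lists its time points as baseline and years 1, 2 and 3. The Aim 1A analysis fits linear and curvilinear trajectories over three years. The Aim 2A primary analysis models effects "on baseline CF and SI and on changes over 36 months, accounting for random neighborhood-level variance".

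**A related mismatch.** The abstract says that "participants will complete baseline visits to collect demographics, health history, and health measurements (e.g., blood pressure, body mass index" and similar measures are taken there. Table 1 and the Physical exam measures section start blood pressure, height and weight at T1.

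**The concern.** The analysis sections use outcome values that the schedule does not collect. Three things follow if this stays unreconciled.

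- A T1 value could be reported as a baseline value, and a change over 30 months as a change over 36.
- A model with time coded from T0 would report an intercept six months before the first outcome observation.
- Outcome data exist only for people who remain to T1. Loss between T0 and T1 removes a participant from every outcome analysis, but the text gives no sign that it is to be counted that way.

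**Working it through.** **1. Is there any outcome value at T0?** The narrative schedule, Table 1 and the measures sections agree that there is not, so this is not a misread table. The only earlier cognitive information is in the screening section: the Mini MoCA, with exclusion below 12, and one question on worsening memory. The Mini MoCA is a different scale from MoCA and Cognigram, is truncated by the eligibility rule, and is not named as an outcome or baseline covariate. No social isolation scale is given before T1.

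**2. Could baseline mean T1?** No section says so. Reading Aim 2a's years as follow-up years, year 3 after T1 would fall at month 6 + 36 = 42, and the schedule ends at month 36. With T0 as baseline, the baseline outcome is missing; with T1 as baseline, year 3 is missing. Aim 2a's time points cannot be met either way.

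**3. The plan's own figures.** Aim 1b: 5 communities × 10 block groups × 20 people = 1,000. Attrition: 1,000 / (1 − 0.08) = 1,087. Both reproduce. Neither depends on the visit schedule, and the power text states no number of occasions and no slope estimand.

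**4. Information on a linear slope.** With residual variance σ², the residual part of one person's slope variance is σ²/Sxx, where Sxx is the sum of squared visit times about their mean.

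- T0 to T6 (0, 6, …, 36; mean 18): Sxx = 2 × (18² + 12² + 6²) = 1008.
- T1 to T6 (6, 12, …, 36; mean 21): Sxx = 2 × (15² + 9² + 3²) = 630.
- Ratio of residual parts: 1008 / 630 = 1.60.

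Let between-person slope variance be k times the 7-occasion residual part, σ²/1008. The variance of a mean slope is then inflated by (k + 1.6)/(k + 1). The documents do not give k, so these values are assumptions:

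| k | Variance ratio | SE ratio |
|---|---|---|
| 0 | 1.60 | 1.265 |
| 1 | 2.6 / 2 = 1.30 | 1.140 |
| 4 | 5.6 / 5 = 1.12 | 1.058 |

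**5. Where the intercept is placed.** The residual variance of a fitted level at time t₀ is σ² × [1/n + (t̄ − t₀)²/Sxx].

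- Month 0, with T0 data: 1/7 + 18²/1008 = 0.464 σ².
- Month 0, as scheduled (extrapolated): 1/6 + 21²/630 = 0.867 σ².
- Month 6 (T1), as scheduled: 1/6 + 15²/630 = 0.524 σ².

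On the present schedule a level at T1 is supported by data and is much better determined than one at month 0.

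**The case against.** The strongest reply is that this is mainly labelling. Growth models estimate an initial level and a trajectory from six occasions. Table 1 itself footnotes T0 as the screening visit. The abstract can be read as attaching outcome assessment to the six-month follow-ups. Aim 2a's list of years may reflect the years for which neighborhood measures are computed. In a cohort of existing residents no exposure begins at T0, so T0 would not be an unexposed baseline either. Most of this stands. It limits the harm, but it does not supply a T0 outcome or a definition of baseline as T1.

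A reader might infer four stronger things that the documents do not support:

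- **That the study cannot estimate levels or trajectories.** It can, over months 6 to 36. What is missing is an observed month-0 level and an observed 36-month change.
- **That a full burn season passes before the first outcome.** The Setting section puts burning at about October to May, longer than the six months from T0 to T1. The shorter non-burn season could fit inside that gap, but only for a limited range of T0 dates.
- **That the 8% attrition allowance leaves out loss before T1.** The sample size text does not say. Dividing by 0.92 treats each lost person as contributing nothing, which is compatible with loss before T1.
- **That power falls by a known amount.** The 7-occasion comparator is not an assumption of the power text, and 26% is an upper bound. The sum of squares for linear time also does not measure the precision of the seasonal PM2.5 effect in Aim 1A.

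**Conclusion.** The concern holds as a contradiction between the schedule and the analysis. Aim 1a, Aim 2a and the Aim 2A primary analysis are written for outcome values at T0 and a 36-month change, while the schedule yields 6 occasions over 36 − 6 = 30 months. As written, the stated Aim 2A primary analysis cannot be carried out on observed data.

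Relative to a design that also tests at T0, the standard error of a linear slope is between about 6% and 26% larger over the range of k examined. This assumes complete, equally spaced visits and independent residuals with constant variance; the top figure also assumes no between-person slope variance. It describes what the missing occasion costs, and does not show that the study is underpowered. The conclusion on labelling and follow-up length needs none of these assumptions. Whether the 8% allowance includes T0 to T1 loss remains open.

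**What to change.** 1. Define T1 as the outcome baseline and code time from T1. State outcome follow-up as 30 months in Aims 1a and 2a and in the Aim 1A and Aim 2A analyses, and restate Aim 2a's time points as visits that exist.
2. Report loss between T0 and T1 as outcome attrition, and say whether the 8% allowance includes it.
3. Make the abstract's placement of blood pressure and BMI agree with Table 1 and the Physical exam measures section.

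These steps cost wording only and make the stated follow-up slightly shorter.

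Optionally, give the outcome instruments at T0 to participants not yet enrolled. Enrolment began in January 2024, so the schedule, and with it practice at a given visit, would then differ by enrolment date. The model would need a term for the number of prior test administrations. The further cost is a longer T0 visit, and people already enrolled gain nothing from it.

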### Ethical considerations and declarations

The RRR study is funded by a U.S. National Institute on Aging grant (R01AG083925). The planned human subjects research has been approved via Florida Atlanta University’s (FAU) Institutional Review Board (IRB), which is the single IRB (sIRB) that is relied upon by the collaborating institutions (University of Miami, Washington State University, University of Arizona, and Colorado State University).

### Study measures at baseline visit (T0)

#### Sociodemographics and health survey

Participants will be asked for their contact information, years living in their community, and basic demographics (e.g., gender, race/ethnicity, educational attainment, country of birth, preferred language, marital status, and religion). The survey will also ask about their household and housing/rental characteristics (e.g., living situation, number in household, home ownership/renting status, housing type, receipt of rental assistance or social security disability), their economic status (e.g., household income, employment/retirement information including whether in sugar cane fields), and primary transportation mode. Participants will be asked about their digital literacy and technology use and access (WiFi, computer, smartwatch/wearable fitness tracker). They will be asked about their health and insurance use/access and pre-existing health behaviors and conditions (i.e., smoking, asthma, chronic obstructive pulmonary disease, chronic cough, high blood pressure, heart disease, diabetes, stroke, sleep problems, head injury, hearing or vision loss, physical limitations). Lastly, participants will be asked about their physical activity frequency including how much is completed outdoors, and whether they feel safe walking in the dark in their neighborhood.

### Study measures at follow-up visits (T1-T6)

#### Sociodemographics and health survey

At the T1-T6 visits, the shortened survey will re-ask about contact information, marital status, living situation, household characteristics, employment/retirement status and details, digital literacy, technology access and use, main transportation mode and car ownership, health care and insurance use/access, smoking status, physical activity frequency, physical limitations, and history of chronic conditions. Participants will also be asked about any change in educational attainment.

#### Cognitive measures

At the T1 to T6 visits, participants will report whether they experienced worsening of their memory. Cognitive testing will include the Montreal Cognitive Assessment (MoCA) [46], a global cognition screening instrument with scores ranging from 0 to 30 with lower scores indicating greater impairment. A score of 26 or above is generally considered normal, while lower scores may indicate cognitive impairment. In addition, the Cognigram will assess four cognitive domains [psychomotor function, attention, learning, and working memory) [47, 48]. A score of < 90 on learning/working memory composite and ≥ 90 on attention/psychomotor composite indicates risk of mild cognitive impairment (MCI).

#### Physical exam measures

At the T1 to T6 visits, systolic and diastolic blood pressure and height and weight will be measured. Blood pressure will be measured by oscillometer, and high systolic blood pressure (SBP) will be defined as values ≥140 mmHg. Measured height and weight will be used to calculate BMI (kg/m^2^), with BMI values of >30kg/m^2^ indicative of obesity.

#### Alcohol consumption

At the T1, T3, and T5 visits, participants will be asked about their alcohol use using the AUDIT-C (alcohol consumption), a brief, reliable, and valid screening tool for alcohol use consisting of three questions [49]. The first question “How often do you have a drink containing alcohol?” is answered on a Likert Scale from never to ≥4 times a week. If participants answer “never”, the screening ends and they receive a total score of 0. Otherwise, two additional questions will be asked about the amount of alcohol consumed: “How many on a typical day when drinking” (1 to 10 or more), and “How often do you have five or more drinks on one occasion?” answered “Never” to “Daily or almost Daily”. A score of 3 or more or reporting 6 or more drinks in a single occasion indicates risk for alcohol use disorder.

#### Psychosocial measures

At the T1 to T6 visits, the PROMIS Social Isolation 4a [50], Lubben Social Network Scale-6 (LSNS-6) [51], Berkman-Syme Social Network Index (BSNI) [52], and De Jong Gierveld Loneliness Scale will assess social isolation, social connectedness, and social networking, and loneliness, respectively [53].

PROMIS Social Isolation 4a: A brief tool with evidence of validity and reliability (Coefficient alpha > 0.90) assessing social isolation over the past seven days with four items (e.g., feel left out) rated from 1 (Never) to 5 (Always). The total score ranges from 4 to 20, with higher scores indicating greater social isolation.LSNS-6: An instrument with evidence of validity and reliability (Coefficient alpha > 0.80) assessing social engagement through six items (e.g., number of relatives see/hear from at least once a month) scored from 0 to 5. The total score ranges from 0 to 30, with lower scores indicating greater social engagement.BSNI: An instrument with evidence of validity and reliability (Coefficient alpha = 0.79), assessing social connectedness through 11 items (e.g., frequency attending religious meetings/services) measuring four types of social connections, including marital status (married versus not), sociability (number and frequency of contacts with children, close relatives, and close friends), church group membership (yes versus no), and membership in other community organizations (yes versus no). Scores range from 0 to 4, with higher scores indicating greater connectedness.De Jong Gierveld Loneliness Scale: An instrument with evidence of validity and reliability (Coefficient alpha ≥ 0.70–0.76) instrument that collects 6 items (e.g., miss having people around) that measure overall loneliness, including emotional and social loneliness, with responses ranging from "*yes*" to "*more or less*" to "*no*." The total score ranges from 0 to 6, with higher scores indicating greater loneliness.

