#### Aim 1A

General linear mixed model (GLMM) analyses with year and season nested in participants within neighborhood block groups will be conducted for Aim 1A to evaluate the effects of changes in PM_2.5_ averaged over burn and non-burn seasons, as well as other temporal integration windows, on CF and SI. Controlling for random variance in outcomes across neighborhood block groups protects against inflated Type I errors due to neighborhood-level intraclass correlations. Additionally, linear and curvilinear trajectories for CF/ADRD risk and SI over the 3-year period associated with PM_2.5_ levels will be assessed using multilevel linear growth modeling. Both time-varying (e.g., health behaviors, work and home environments, comorbidities) and time-invariant (e.g., sex) individual- and neighborhood-level covariates (see Fig 1) will be incorporated into prediction models to control for these additional individual and neighborhood/community influences on the outcomes.

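### The stated direction of the LSNS-6 score conflicts with the article's own description of its items, so LSNS-6 results could be reported the wrong way round

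*Protocol article*

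**What the plan says.** The protocol article, under Psychosocial measures, lists four instruments given at visits T1 to T6: PROMIS Social Isolation 4a, LSNS-6, BSNI and the De Jong Gierveld scale. Together they "will assess social isolation, social connectedness, and social networking, and loneliness, respectively".

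The LSNS-6 is described as "assessing social engagement through six items (e.g., number of relatives see/hear from at least once a month) scored from 0 to 5". The next sentence gives its range and direction: "The total score ranges from 0 to 30, with lower scores indicating greater social engagement".

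The other three directions are:

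- PROMIS Social Isolation 4a: "The total score ranges from 4 to 20, with higher scores indicating greater social isolation".
- BSNI: "Scores range from 0 to 4, with higher scores indicating greater connectedness".
- De Jong Gierveld: "The total score ranges from 0 to 6, with higher scores indicating greater loneliness".

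Social isolation (SI) is an analysed outcome beside cognitive function (CF). The Aim 1A analysis, for example, looks at seasonal averages of PM2.5 "as well as other temporal integration windows, on CF and SI", and Aims 1B, 2A and 2B use the same pair of outcomes. No other section gives an LSNS-6 direction or mentions reverse coding.

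**The concern.** A scale said to measure engagement, built from items such as a count of contacts, should rise as engagement rises. The article says that it falls. This is a positive statement of a scoring rule that disagrees with the preceding sentence, so it is not simply detail left out of a condensed article.

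What is at stake is interpretation. The four scales already run in different directions, so an analyst has to rely on the text to know which way each one points. Someone who sums the LSNS-6 items in the ordinary way and then reads the total through this sentence would take more contact for less engagement. An exposure that reduces contact would then be written up as increasing engagement. The same inversion would reach the race/ethnicity interactions of Aims 1B and 2B wherever LSNS-6 is the outcome.

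**Working it through.** **Inputs**, all from Psychosocial measures: six items; each scored 0 to 5; example item a number of relatives in contact; total 0 to 30; stated direction, lower means more engaged.

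**Step 1: reproduce the range.** The total is T = sum of six items.

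- Minimum = 6 × 0 = 0
- Maximum = 6 × 5 = 30

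This matches the stated 0 to 30, so the total is consistent with a plain sum.

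**Step 2: direction of the plain sum.** If each item rises with the count it records:

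- fewest contacts: 6 × 0 = 0
- most contacts: 6 × 5 = 30

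The total rises with engagement, which is the opposite of the stated direction.

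**Step 3: what would make the stated direction true.** Every item would have to be reversed, scored as 5 minus the item:

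- fewest contacts: 6 × (5 − 0) = 30
- most contacts: 6 × (5 − 5) = 0

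The range is again 0 to 30, so the range alone cannot separate the two codings. The item description can, and it mentions no reversal.

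**Step 4: when a wrong conclusion follows.** As an illustration, suppose an exposure lowers contact by one category on each item.

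| Items scored | Change in total | Read as stated (lower = more engaged) | Read as higher = more engaged |
|---|---|---|---|
| In the direction of the count | 6 × (−1) = −6 | engagement up: **wrong** | engagement down: right |
| Reversed | 6 × (+1) = +6 | engagement down: right | engagement up: **wrong** |

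The error needs coding and interpretation to disagree. The top-left cell is the one that the article's text invites.

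**Step 5: size.** The reversed total is 30 − T, so any linear association with it has the same magnitude and the opposite sign. An illustrative simulation with assumed data (n = 1,000) agreed: the correlation with latent isolation was −0.92 for the plain sum and +0.92 for the reversed one. Only the sign differs.

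**Step 6: set beside the other scales.**

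| Scale | A higher score means |
|---|---|
| PROMIS Social Isolation 4a | more isolated |
| De Jong Gierveld | more lonely |
| BSNI | more connected |
| LSNS-6, as stated | less engaged |
| LSNS-6, as its items imply | more engaged |

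As its items imply, LSNS-6 runs with the BSNI, the other scale that draws on contacts. As stated, it runs with PROMIS and De Jong Gierveld, and an analyst aligning the four scales from this text would turn it the wrong way.

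**The case against.** The strongest defence is that the article does not print the response anchors, so it never says which category scores 0 and which scores 5. An undescribed reversal is therefore not strictly excluded. If the items were both coded and read in the stated direction, nothing would be wrong. That stands as a limit on certainty, but it does not make the passage consistent. A single slip, *lower* for *higher* or *engagement* for *isolation*, is the likelier explanation.

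A reader might infer several stronger things that the document does not support:

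- **That every LSNS-6 coefficient will have the wrong sign.** A coefficient from the raw total is the same number whatever this sentence says. Only its interpretation or alignment can flip.
- **That the scoring code is wrong.** No scoring code is described. REDCap appears only for consent, the recording of interest in the substudies, and data entry and storage.
- **That LSNS-6 would cancel the other scales in a combined score.** No composite of the four scales is planned in the article. The analysis sections speak only of SI and do not say which instrument represents it.
- **That every aim is affected.** The Aim 3 target variables are EMA responses, n-back scores and ADRD risk scores, and LSNS-6 is not named among them.
- **That all four are social-isolation measures in the strict sense.** The article assigns them to isolation, connectedness, networking and loneliness, although all sit in the same psychosocial section.

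It can also be said that this is one word in an instrument description and can be corrected without losing data. That is true, and it bears on how cheap the remedy is. The sentence is nevertheless the only statement of the scoring direction for an instrument in a named outcome domain.

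**Conclusion.** The point holds as an internal contradiction. The described items give a total that rises with engagement, and the stated direction is the reverse. If totals are summed as described and interpreted or aligned as stated, LSNS-6 associations with PM2.5 or neighbourhood exposures in Aims 1 and 2 would be reported in the wrong direction. Magnitudes, sample size and power do not change.

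This rests on two assumptions: that the example item is typical of the six, and that no unreported reverse coding is used. The effect on results also depends on a mismatch between coding and reading, and on LSNS-6 being used as an SI outcome in those models. The article establishes neither.

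**What to change.** 1. Correct the LSNS-6 sentence to say that higher scores indicate greater social engagement and lower scores greater isolation. If the items are in fact reverse-coded, keep the direction and state the reverse coding explicitly.
2. Check that the scoring code matches the corrected sentence. This is a check and presumes no fault.
3. Label the direction of each of the four psychosocial scales wherever they are modelled or reported. Turning all four the same way is one convention; reporting each in its own labelled direction serves equally well.

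The cost is one sentence, one check of the code and clear labels. No design change or new data are needed. A total found to be stored in the opposite direction can be converted as 30 minus the total. Enrolment began in January 2024, so the check is best done before any LSNS-6 model is fitted.
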